### **9.7 Sample size estimation**

The study population will comprise up to 400 subjects 18 years and older, who fulfil the inclusion criteria, and do not meet any of the exclusion criteria who will be randomised into 6 groups of 65 subjects per group. The TGA based on long standing experience with influenza vaccines requires a minimum group size of 50 subjects per group for assessment of influenza vaccine antibody responses for vaccine release purposes. Therefore, rather than using a power calculation based on our own limited assumptions, we have instead relied upon this TGA requirement as our guide in designing the group size for this study, further allowing for a 20% drop out rate for subjects failing to attend for the final blood sample, thereby ensuring we meet the TGA minimum group size.

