### **5.2 Choice of control groups and blinding**

This is a randomized, controlled Phase 2 study. A total of up to 400 subjects will be recruited for the study, and randomly assigned on a one to one to one basis (1:1:1) to standard TIV, TIV + Advax 5mg or TIV + Advax 10mg. All subjects will also be randomised on a 1:1 basis to receive the immunisation via needle and syringe or Pharmajet needleless injector device. There will therefore be 6 subgroups in total.

As the vaccine containing Advax is a cloudy white colour whereas TIV is a clear solution, it is not possible for the staff administering the vaccine to be blinded. Subjects will be blinded and will not be informed which vaccine they receive. Similarly, where a trial adverse effect requires assessment, this will be performed by a blinded adjudicator. All laboratory tests will be performed blinded.

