### **6.3 Replacement policy**

Individuals dropping out of the study prior to Visit 3 will be replaced at the discretion of the Principal Investigator.

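### Section 9.7 presents an expected 52 evaluable subjects per group as a guarantee of 50 in each of six groups; at a true 20% loss without replacement, all six reach 50 with probability of about 0.23

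*Protocol*

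**What the plan says.** Protocol section 9.7 sets aside a power calculation and takes its group size from a regulatory requirement: the TGA "requires a minimum group size of 50 subjects per group for assessment of influenza vaccine antibody responses". Subjects are to be "randomised into 6 groups of 65 subjects per group", "further allowing for a 20% drop out rate for subjects failing to attend for the final blood sample", and the section concludes "thereby ensuring we meet the TGA minimum group size".

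The total is capped: "The study population will comprise up to 400 subjects 18 years and older". Section 5.2 explains the six groups as three formulations crossed with two injection methods: "There will therefore be 6 subgroups in total".

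Section 6.3 gives the only other protection against loss: "Individuals dropping out of the study prior to Visit 3 will be replaced at the discretion of the Principal Investigator". The visit schedule in section 4.1.1 gives a number to Visit 1 only; the later contacts are identified by study day.

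**The concern.** The minimum of 50 per group is the whole stated basis for the sample size, so the claim that it will be met carries the justification. Section 9.7 attaches the minimum to the six randomised groups. Dividing the target by one minus the drop-out rate gives a group size whose expected number of completers meets the target. It does not give a size at which every group will meet it. With six groups the smallest is likely to fall below the average, and the planned margin is two subjects.

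At stake is the accuracy of a design property that readers and the ethics committee are asked to rely on. No section attaches a decision rule to a group ending below 50, so a shortfall would not by itself invalidate any planned analysis.

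**Working it through.** **Inputs (Protocol).**
- 65 randomised in each of 6 groups, so 6 × 65 = 390 (section 9.7)
- Minimum of 50 per group (section 9.7)
- Drop-out of 20%, meaning the final blood sample is missed (section 9.7)
- Cap of 400, leaving 400 − 390 = 10 spare places (sections 6 and 9.7)

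**The plan's own figure.** 50/(1 − 0.20) = 62.5, rounded up to 63. The plan takes 65, and 65 × 0.80 = 52 completers are expected. The inflation is sound and slightly generous.

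**One group.** Let X be the number of completers among 65, with X ~ Binomial(65, 0.80) if subjects drop out independently and the true loss is 20%. Then P(X ≥ 50) = 0.7846, so a group falls short about one time in five.

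**All six groups.** With independent groups and no replacement, 0.7846^6 = 0.233. The chance that at least one group falls short is 1 − 0.233 = 0.767.

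**Sensitivity to the loss rate, 65 per group.**

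| True loss | Expected completers | P(one group ≥ 50) | P(all six ≥ 50) |
|---|---|---|---|
| 10% | 58.5 | 0.9995 | 0.997 |
| 15% | 55.25 | 0.972 | 0.841 |
| 18% | 53.3 | 0.888 | 0.489 |
| 20% | 52.0 | 0.785 | 0.233 |
| 25% | 48.75 | 0.424 | 0.006 |

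**Filling the cap evenly at 20% loss.** 400 subjects make four groups of 67 and two of 66. The single-group probabilities are 0.8923 and 0.8452, so 0.8923^4 × 0.8452^2 = 0.45.

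**Best case for replacement at 20% loss.** Suppose all 10 spare places go to whichever groups are short, and the replacements are themselves lost at 20%. By simulation, all six groups then reach 50 with probability of about 0.92.

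**High assurance from enrolment alone at 20% loss.** 90% for all six groups needs 72 per group (6 × 72 = 432), and 95% needs 73 (6 × 73 = 438). Both exceed 400.

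**Formulations pooled over device.** 2 × 65 = 130 randomised and 130 × 0.80 = 104 expected. P(at least 50) is 1 to many decimal places.

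**The case against.** The strongest reply is that nothing has been miscalculated. The inflation is the standard one, and the plan rounds up beyond what it needs. Allowing for 20% can be read as a cautious ceiling in a trial with one injection and a last visit at Day 28; at 10% or 15% loss all six groups probably reach 50. Replacement is permitted, and used as well as it could be, it lifts the figure at 20% loss to about 0.92. Section 9.7 also calls the TGA figure a guide, and section 9.4 compares adjuvanted with unadjuvanted and needle with needleless groups, where numbers are far larger than 50.

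Much of this stands. It rules out calling the calculation an arithmetic error, and it rules out quoting 23% without its conditions. It does not rescue the guarantee. The text does not say that 20% is a ceiling, and at 20% itself the claim fails. The 0.92 requires all spare places to go to the short groups in time. Section 6.3 does not require this: replacement is discretionary, and its cut-off is a visit that the schedule does not define. If that visit falls before Day 28, the rule does not reach subjects who miss only the final sample, which is the loss that section 9.7 names.

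A further reply is that section 9.2.2 admits subjects with any post-baseline antibody measurement, and section 8.7.2 also plans a Day 7 sample from everyone. But the primary endpoint in section 2.1 is measured at 21–28 days, which a Day 7 titre does not supply.

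A reader might also infer that discretionary replacement lets the investigator select who enters which arm. The protocol does not support that. Sections 8.3 and 9.10 describe allocation in order of enrolment from an independently generated sequence, with codes held away from the site. The discretion is over whether to replace, not over allocation. Section 5.2 says that staff giving the vaccine are unblinded; it does not say this of the Principal Investigator.

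**Conclusion.** The point holds as an overstated assurance. The group size of 65 follows correctly from 50 and 20%, but it supports an expectation of 52 per group and not a guarantee of 50 in all six. The figure of 0.23 assumes a true loss of exactly 20%, independent drop-out, 65 per group and no replacement. Relaxing these assumptions gives 0.45 with 400 enrolled evenly, about 0.92 under ideally targeted replacement, 0.84 at 15% loss and 0.997 at 10%. A loss above 20% makes it worse.

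It would be tempting to conclude that the trial is too small or that a group will fail the TGA requirement. The protocol does not support either: the actual loss is unknown, the planned formulation and device comparisons pool across groups, and each pooled formulation group passes 50 with near certainty. The consequence is confined to the wording of the sample-size justification, which should be corrected because it is the only justification given.

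**What to change.** In section 9.7:

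1. Replace the word *ensuring* with a statement that about 52 evaluable subjects per group are expected at 20% drop-out.
2. State the probability that all six groups reach 50 and its assumptions: about 0.23 at 20% loss with independent drop-out and no replacement, and higher at lower loss (0.84 at 15%, 0.997 at 10%).
3. Note that each formulation pooled over device, with 130 randomised and about 104 evaluable, exceeds 50 with near certainty.

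Two further changes may suggest themselves but should not be made. Deleting replacement from section 6.3 would remove the only mechanism that raises the chance of reaching 50. Moving the TGA minimum from the six groups to the three formulations would leave 390–400 subjects without their stated basis, since 3 × 63 = 189 would then suffice. The third item is therefore information for the reader and not a new target.

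The cost is wording only. No subjects are added; the downside is a less favourable stated figure.

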### **9.8 Subgroup analyses**

A pooled efficacy analysis will be performed on the total study efficacy population. In addition, subgroup analyses of vaccine response rates will be performed stratifying responses according to the subject age and analysis of differences in GMT by ANOVA and seroconversion and seroprotection rates by Fishers exact test.

### **9.9 Data handling and quality assurance procedures**

Accurate and reliable data collection will be assured by verification and cross-checking of the CRF against the investigator’s records by the study monitor, and the maintenance of a drug dispensing log by the investigator. All correspondence between investigators and study monitors addressing apparent inconsistencies or to clarify entries on the CRF will be kept on file at the site. The data entry group will enter data from the working copy of the CRF (retrieved from the centre) into a computer database.

### **9.10 Randomisation procedure**

Random allocation sequences will be generated by an independent source. . Randomisation codes will be held independently to the site. To randomise a subject the investigator or study co-ordinator will use an on-line interface to enter subject initials and date of birth. On entering this data, they will be issued with the next available randomisation code for the particular randomisation block or category to which the entered subject belongs, e.g. with or without Advax, 10mg or 20mg etc.

## **10. DRUG SAFETY**

### **10.1 Definition of adverse events and SAEs**

#### **10.1.1 Adverse event**

An adverse event is defined as:

Any untoward medical occurrence in an individual or clinical investigation subject who has been administered a pharmaceutical product and which does not necessarily require a causal relationship with the treatment. An adverse event can therefore be any unfavourable and unintended sign (including an abnormal laboratory finding, for example), symptom, or disease temporarily associated with the use of a medicinal product, whether or not considered related to the medicinal product.

Specifically, adverse events include:

1. All unfavourable changes in general condition.
2. All subjective or objective symptoms.
3. All concomitant diseases or accidents.
4. All clinically relevant changes in laboratory parameters.

Post-immunisation adverse events will be specifically defined as those adverse events occurring in the first 28 days post-immunisation. However, adverse event data will continue to be collected for the duration of the study follow-up period of 1 year post-immunisation

#### **10.1.2 Serious adverse event**

An SAE (or experience) or reaction is any untoward medicinal occurrence that at any dose:

1. Results in death.
2. Is life-threatening
3. Requires an individual's hospitalisation or prolongation of existing hospitalisation (over and above the period of hospitalisation foreseen in the protocol).
4. Results in persistent or significant disability/incapacity.
5. Is a congenital anomaly/birth defect.

(Note: the term "life-threatening" in the definition of "serious" refers to an event in which the individual was at risk of death at the time of the event; it does not refer to an event which hypothetically might have caused death if it were more severe).

The term "severe" is often used to describe the intensity (severity) of a specific event (as in mild, moderate or severe myocardial infarction); the event itself, however, may be of relatively minor medical significance (such as severe headache). This is not the same as "serious", which is based on individuals/event outcome or action criteria usually associated with events that pose a threat to an individual's life or functioning. Seriousness (not severity) serves as a guide for regulatory reporting obligations. Any death occurring during the study or which comes to the attention of the investigator within 4 weeks after stopping the treatment, whether considered treatment-related or not, must be reported. In addition, drug misuse or drug overdose should be regarded as an SAE, even if they may not result in the above mentioned outcomes. All SAEs must be reported immediately according to the guidelines for subsequent reporting to the appropriate regulatory authorities. The investigator must notify the Ethics Review

Committee of such an event in writing as soon as it is practical and in accordance with international and local laws and regulations.

### **10.1.3 Unexpected Adverse Event**

An experience not previously reported (in nature, severity or incidence) in the current Investigator's Brochure as provided, is defined as an unexpected adverse event.

### **10.1.4 Methods of recording and assessing adverse events**

All adverse events must be documented in the section of the CRF reserved for this purpose and not in remarks elsewhere in the CRF. The following aspects must be recorded

- The onset.
- Where applicable, the end of the adverse event.
- A description of the adverse event.
- Any factors considered as possibly promoting the occurrence of the adverse event.
- Concomitant medication.

An assessment by the investigator of the causality; the decisive factor in the documentation is the temporal relationship between the adverse event and the study drugs. The following judgments of the causal relationship are possible: none, remote, possible, probable and not assessable. If, in any individuals, the same adverse event occurs at several investigational times, then the adverse event in question must be documented and assessed anew each time.

Participants will be monitored by study staff for 30 min after immunization for any immediate adverse events and by the subjects themselves using a symptom diary for 28 days post immunization. Participants will be instructed to assess specific injection site adverse events (redness, swelling, warmth, tenderness, pain with arm movement) and systemic adverse events (chills, headache, muscle aches, fatigue, nausea, vomiting, diarrhoea, joint pain), all reports of other adverse events will be collected and categorized by body system. Adverse events will be collected by study personnel at each visit.

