Adjuvants are a critical ingredient for many vaccines and act by boosting the immune response to vaccine antigens (e.g. influenza vaccine antigens). Despite considerable research, aluminium salts (alum) remain the dominant adjuvants used globally in human vaccines and there is a major need for new adjuvants, in particular, for adjuvants capable of boosting cell-mediated immunity (this is a particular type of immune response where T cells are activated that are then able to attack and destroy the infection). Alum, although good at stimulating antibodies, is poor at stimulating cell-mediated immunity. The majority of current commercial subunit flu vaccines, including those marketed in Australia do not contain an adjuvant.

FLUAD is a subunit influenza vaccine marketed by Novartis in Europe which contains a squalene oil adjuvant known as MF59. MF59 has been shown in clinical trials to induce higher influenza antibody titres when combined with seasonal or pandemic vaccines, albeit at the cost of higher local and systemic reactogenicity as reflected in

increased injection site pain, headaches and fever. Clinical data accrued to date suggests that Advax™ adjuvant may deliver similar benefits to MF59 adjuvant but without the propensity of MF59 to cause adverse reactions.

Advax™ adjuvant is manufactured under GMP from inulin, a natural storage polysaccharide of plants such as chicory and dahlias. Inulin in its soluble form is already approved in many countries for human intravenous use for renal function testing and is known to be an extremely safe and nontoxic compound. When crystallised, inulin develops properties including an ability to enhance the immunogenicity of co-administered vaccine antigens, which forms the basis for its use as a vaccine adjuvant. Previous clinical studies performed at FMC have confirmed the effectiveness and safety of Advax™ adjuvant when formulated with hepatitis B surface antigen, seasonal or pandemic influenza antigens or bee venom antigen. These studies all support the safety, tolerability and efficacy of Advax™ adjuvant in humans.

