#### **5.1.2 Elicited Local symptoms/signs**

- ☐ -pain, tenderness, erythema/redness, induration/swelling
- ☐ Vital signs
- ☐ -fever, tachycardia, bradycardia, hypertension (systolic/diastolic), hypotension, increased respiratory rate

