#### **8.5 Follow-up**

The assessments that should be conducted at these visits are given in the Schedule of Assessments. The following evaluations will be performed.

1. Vital signs (blood pressure, heart rate, temperature).
2. Inspection of immunization site
3. Blood sample for influenza antibodies and T-cell responses and safety tests where indicated.
4. Adverse event history.

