All enrolled individuals who received at least one dose of treatment will be included in the safety population. The analysis will include listings and frequency tables of adverse events and laboratory values graded according to the FDA/CBER vaccine toxicity grading scale. Adverse events will be tabulated by time (day) and by severity (mild, moderate and severe). Clinically significant reactions will be defined as measured local reactions >10mm, fever >38°C and severity  $\geq$  moderate for other symptoms. Severe reactions are defined as measured local reactions >50mm, fever >39°C and severity  $\geq$  severe for all other symptoms. Injection site reactions will be combined to give an “any local” reaction category and all other symptoms combined to give an “any general” reaction. The proportion of subjects having an adverse reaction will be estimated by vaccine group, observation period and severity. Subjects will be asked to score injection site pain at the time of injection, and 30 minutes post immunization using a visual analogue scale. Binomial distribution point estimates and 95% confidence intervals will be used to estimate each rate. Percentages will be compared by Fishers exact test.  $P < 0.05$  will be considered statistically significant. No adjustments will be made for multiple comparisons.

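### Fever and local reactions are graded by measurement in section 9.6, but the list that subjects are told to assess omits fever and asks for no measurement

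*Protocol*

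**What the plan says.** **What the analysis uses.** Protocol section 9.6 sets two measured grades. The lower reads "Clinically significant reactions will be defined as measured local reactions >10mm, fever >38°C" and the higher "Severe reactions are defined as measured local reactions >50mm, fever >39°C". Other symptoms are classed by severity alone. The same section states: "Adverse events will be tabulated by time (day) and by severity (mild, moderate and severe". Rates get 95% confidence intervals, and percentages are compared by Fisher's exact test. Adverse events and tolerability are a primary endpoint.

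**What is meant to be elicited.** Section 5.1 collects specified solicited events for 7 days. Section 5.1.2 includes, under vital signs, "fever, tachycardia, bradycardia, hypertension (systolic/diastolic), hypotension, increased respiratory rate".

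**What subjects are told to assess.** Section 10.1.4 provides for 30 minutes of staff observation and then a 28-day symptom diary. Subjects assess redness, swelling, warmth, tenderness and pain on moving the arm, together with "systemic adverse events (chills, headache, muscle aches, fatigue, nausea, vomiting, diarrhoea, joint pain". Reports of other events are also collected.

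**When temperature is taken.** Section 8.5 schedules "Vital signs (blood pressure, heart rate, temperature" at follow-up visits. Section 4.1.1 puts the first clinic visit after vaccination at Day 7, preceded only by an optional Day 1 telephone call.

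**The concern.** The analysis needs a number in °C and a number in mm, tied to a day. The instruction to subjects asks for neither. If staff and subjects follow section 10.1.4 as written, a fever on the first few evenings is not prompted. If it is volunteered, it need not come with a reading that can be set against the 38°C and 39°C cut-offs. Redness and swelling are prompted but not sized, so the 10 mm and 50 mm cut-offs have the same difficulty.

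No later analysis can repair this, because a temperature that was not taken cannot be graded afterwards. Fever also bears on the rationale: section 1.1 contrasts Advax with another adjuvant whose cost is described as "increased injection site pain, headaches and fever".

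**Working it through.** The plan states no figure for fever, so there is nothing to reproduce. The check sets the sections side by side, follows the timetable, and then illustrates the consequence.

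**1. The lists against the analysis**

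| Item | 5.1.2–5.1.3 | 10.1.4 | 9.6 |
|---|---|---|---|
| Fever | listed, under vital signs | absent | °C, cut-offs 38 and 39 |
| Redness, swelling | listed, no unit | listed, no unit | mm, cut-offs 10 and 50 |
| Chills, joint pain, warmth | absent | listed | severity only |
| Pain | pain | pain on arm movement | severity only |

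Fever is thus elicited in one section, graded in a second and missing from the third, which is the one addressed to subjects. No section mentions a thermometer or a ruler.

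**2. The timetable**

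- Day 0: baseline assessment, vaccination, 30 minutes of observation.
- Day 1: optional telephone call; no temperature is specified.
- Day 7: clinic visit, described as a blood-sampling visit. Section 5.3 allows ±7 days, so 7 − 7 = Day 0 to 7 + 7 = Day 14.
- Days 14 and 21: substudy subjects only.
- Day 28: all subjects.

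The solicited window is 7 days. On the nominal schedule no temperature is due between the 30-minute observation and the Day 7 visit. That visit gives a single reading at the edge of the window, or outside it if the visit is late. A single reading cannot fill a table by day.

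**3. Illustration of what under-recording does**

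Inputs: 65 subjects per subgroup (section 9.7), with two subgroups per formulation, so n = 2 × 65 = 130; two-sided 0.05 (section 9.6). The true fever rates r₁ and r₂ and the proportion c of fevers captured are assumptions, because the protocol gives none. Capture is taken as equal in both arms, so the recorded rates are p₁ = c·r₁ and p₂ = c·r₂. With p̄ their mean,

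power ≈ Φ{ [ |p₂ − p₁| − 1.96·√(2p̄(1 − p̄)/n) ] / √( [p₁(1 − p₁) + p₂(1 − p₂)]/n ) }.

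For 5% against 15% at full capture: p̄ = 0.10; √(2 × 0.10 × 0.90/130) = 0.0372; √((0.0475 + 0.1275)/130) = 0.0367; (0.10 − 1.96 × 0.0372)/0.0367 ≈ 0.74, so power is 77%.

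| True rates | c = 100% | 50% | 25% | 10% |
|---|---|---|---|---|
| 5% vs 15% | 77% | 46% | 25% | 13% |
| 3% vs 10% | 63% | 36% | 20% | 10% |
| 2% vs 8% | 60% | 34% | 19% | 10% |

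These are normal approximations before drop-out; Fisher's exact test would give somewhat less. Equal under-recording leaves the ratio of the rates unchanged but shrinks both rates and their difference, so each arm looks better tolerated than it was.

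**The case against.** The strongest reply is that measurement is plainly intended. Section 5.1 promises 7 days of solicited collection, section 5.1.2 names fever among the elicited signs, and section 9.6 speaks of measured reactions with cut-offs. With so few visits, the natural vehicle is the take-home diary, which is not shown and may well hold temperature and size fields. The vital-signs label in section 5.1.2 does not by itself confine fever to clinic visits. Fevers also have other ways in: the diary is for any symptom, the Day 1 call may be made, events are asked about at each visit, and unlisted events are recorded.

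Much of this stands, and it limits the point. A reader might infer that fever will go almost wholly unrecorded and that the trial will then wrongly vindicate the adjuvant. The documents do not support that: the capture routes are real, section 1.1 is worded cautiously, and the comparator here is unadjuvanted vaccine, not the other adjuvant. Nor can one count the fevers that would be missed, since that needs both a fever rate and a capture rate.

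Two further inferences also fail. The any-local and any-general composites in section 9.6 are defined by site, not by either list, so the mismatch affects what is prompted and not the definition. Interference with activity, absent from section 10.1.4, is not lost, because section 10.1.6 uses it to grade severity.

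The reply does not remove the contradiction. A temperature field in the diary would soften the consequence, but section 10.1.4 would still disagree with sections 5.1.2 and 9.6, and none of the routes named requires a reading.

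**Conclusion.** The inconsistency is established from the text: sections 5.1.2 and 9.6 need fever elicited and reactions measured, while section 10.1.4 neither lists fever nor asks for measurement. The solicited lists also differ, with chills, joint pain and warmth only in section 10.1.4 and fever only in section 5.1.

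The consequence is an inference. Early fever is likely to be under-recorded and often ungradable in all arms, and local reaction size is open to the same weakness. How far this goes depends on a diary form that is not shown. The power figures show the direction and the possible scale under assumed rates and equal capture; they are not a forecast.

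This does not threaten the immunogenicity comparison. It does weaken one component of a primary safety endpoint, cannot be recovered later, and should be corrected before enrolment.

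**What to change.** Use one solicited list in sections 5.1.2, 5.1.3, 9.6 and 10.1.4, and include fever in it. State in section 10.1.4 that the diary records a self-measured temperature in °C and the diameter of redness and of swelling in mm, daily through the 7-day solicited window. If the diary already has these fields, the change is one of wording, to bring the sections into line with it.

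The cost is revised diary and protocol text, a thermometer and a ruler card per subject, and a small daily burden for a week. Sample size, visits and analysis methods are unchanged.
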